## Introduction

### Background and rationale

The prevalence of primary chronic daily headaches (CDH) is 5% in the population and is associated with significant morbidity, a poor quality of life, and a substantial burden on the healthcare system [1]. Important subtypes of CDH include chronic migraine, chronic tension-type headache, hemicrania continua, new daily persistent headache, and medication overuse headache [2–5]. Many patients with CDH do not respond to conventional medical management that includes medications, nerve blocks, and psychological approaches, and adverse events with these treatments are also common [6, 7]. Although onabotulinum-toxin A and calcitonin gene-related peptide (CGRP) antagonists are promising new treatments for CDH, these are expensive and their long-term effects are unclear. There is an urgent need for efficacious, safe, inexpensive, and widely available treatments for patients with CDH.

The subtypes of CDH share central sensitization, an increase in neuronal excitability secondary to repetitive stimulation of the nociceptive C-fibers (“wind-up”) in the trigeminocervical complex (TCC) and the brain, as a common mechanism [8–10]. The TCC contains major relay neurons for nociceptive afferent input from the meninges and cervical structures and its sensitization is a key feature of CDH. Central sensitization is mediated primarily by *N*-methyl-d-aspartate (NMDA) receptors. Activation of the NMDA receptors also plays a major role in ongoing pain, opioid-induced hyperalgesia, and mood dysregulation [10]. This sensitization can be reversed on a long-term basis by the blockade of NMDA receptors by non-competitive antagonists such as ketamine [8–10]. Intravenous (IV) ketamine in high doses (0.4 to 1 mg. kg^−1^ .h^−1^) has been used to treat NMDA receptor-driven neuropathic pain syndromes [8].

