### Trial design

The KetHead trial is designed as a multi-center, placebo-controlled, superiority randomized controlled trial with two parallel groups and blinding of participants and outcome assessors. Randomization will take place upon participant enrollment. Randomization will be to one of two arms, with a 1:1 allocation and permuted blocks of six. The randomization sequence will be computer-generated, and allocation concealment will be ensured by sequentially numbered, sealed opaque envelopes. This process will be carried out by an independent research coordinator, who is not involved in the recruitment process or conduct of the trial. An unblinded pharmacist will dispense the trial medication to an unblinded and delegated healthcare provider who will then prepare the trial medication according to protocol and then present it to a blinded physician, who will administer the trial medication according to the protocol. A blinded member of the research team will perform an outcome assessment. Treating physicians, participants, close contacts, trial coordinators, and primary outcome assessors will be blinded to treatment allocation.

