### Sample size

A difference of 3 headache days (standard deviation (SD) of 3.8) in the frequency of headache days between the two groups in the 28 days after the trial infusion is considered as a minimum clinically important difference (MCID) [32] for this trial. A sample size of 25 participants in each group would have over 80% power to detect this difference between the 2 groups using a two-sided alpha of 0.05. Assuming a 10% drop-out rate 1 month after the infusions, 28 participants will be enrolled in each arm. This sample size is also robust to capture a key secondary outcome for this trial—a MCID of 1.0 (SD 1.3) in the mean 0–10 NRS score for average intensity of headaches in the first 28 days after the infusions (power of over 80% with a two-sided alpha 0.05) [14].

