### Statistical methods

The normality of the trial data will be assessed, means and standard deviation (or median and interquartile ranges, as appropriate) will be used to summarize continuous data, and frequencies and proportions will be used for categorical data. To compare data between the 2 groups, categorical outcomes will be analyzed with the chi-square test and continuous variables will be analyzed with independent *t*-tests (or Wilcoxon rank sum test). A baseline-adjusted ANCOVA model will be employed for all outcome variables of interest for which a baseline is recorded in the 28 days interval prior to treatment. In addition, for the primary outcome, an additional ANCOVA model will be employed adjusting for baseline headache days and the following variables that are strongly associated with this outcome: number of headache years, depression/anxiety, intensity of headache, and opioid intake. Estimates of differences in means (with 95% CI) at 28, 56, and 84 days will be provided for continuous outcomes. A Cox proportional hazards model will be built to investigate the effect on variables on the time to a specified event. Missing primary outcome data will not be imputed. A sensitivity analysis assuming the participants lost to follow-up showed no improvement (i.e., they had no change in headache frequency) will then be performed. Group comparisons will be performed in responders (defined as a reduction in pain by 3 or more headache days in 28 days from baseline at 28 days after the infusions) versus non-responders, participants on Botox/CGRP antagonist treatment versus none, comparison across different subtype of CDH, and baseline frequency and average intensity of headaches. An intention-to-treat analysis approach will be used. SAS Studio Edition will be used to conduct the analyses.

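### The planned subgroup comparisons do not test whether ketamine's effect differs between subgroups; treatment-by-factor interactions, read as exploratory, would

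*Protocol article*

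**What the plan says.** After the primary and sensitivity analyses, the Statistical methods section of the protocol article lists group comparisons by response status and then by four baseline factors: "participants on Botox/CGRP antagonist treatment versus none, comparison across different subtype of CDH, and baseline frequency and average intensity of headaches". Response status is defined after treatment; it is a separate matter and is left aside here.

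The methods that section names for comparing the arms are the chi-square test, the independent t-test or Wilcoxon rank sum test, baseline-adjusted ANCOVA, and a Cox model for time to an event. No treatment-by-factor term appears. The section gives no cut-points for frequency or intensity, no list of subtypes to be compared and no significance level for these analyses.

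Two other places bear on the size of the problem:
- Background and rationale: "Important subtypes of CDH include chronic migraine, chronic tension-type headache, hemicrania continua, new daily persistent headache, and medication overuse headache". This is a background statement, not a definition of analysis groups.
- Sample size: "A difference of 3 headache days (standard deviation (SD) of 3.8" is the target difference, tested "using a two-sided alpha of 0.05". The section adds "A sample size of 25 participants in each group would have over 80% power" and "28 participants will be enrolled in each arm".

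**The concern.** The question a subgroup analysis should answer is whether the ketamine-placebo difference changes with a baseline characteristic. The sentence can be read in two main ways, and neither answers it.

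- **Tests inside subsets.** The arms are compared among Botox/CGRP users, then among non-users, and so on. A significant result in one subset and a non-significant result in the other is not evidence that the effects differ. In small subsets it mostly reflects size and chance.
- **Contrasts between subsets.** Users are compared with non-users, or one subtype with another. That describes prognosis and says nothing about effect modification.

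At stake is what readers conclude about who benefits. The trial enrols several headache types, so a statement that ketamine works in one type and not in another would be noticed, and this design could easily produce one by chance.

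**Working it through.** **Inputs.** From Sample size: difference 3 days, SD 3.8, two-sided alpha 0.05, 25 evaluable and 28 enrolled per arm, "Assuming a 10% drop-out rate 1 month after the infusions". From Trial design: "with a 1:1 allocation and permuted blocks of six". Assumed, because the document does not state them: 0.05 for each subgroup test, median splits for frequency and intensity, two to five subtypes, and 30% or 50% Botox/CGRP users.

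**1. The plan's own figure.**
- n per arm = 2 × (1.960 + 0.842)² × 3.8² / 3² = 25.2, rounded up to 26. The stated 25 is within one.
- Power at 25 per arm: SE = 3.8 × √(2/25) = 1.075 and 3/1.075 = 2.79. This gives 79.7% by the normal approximation and 78.1% by the noncentral t, close to the stated level though just under it.
- Drop-out: 25/0.90 = 27.8, so 28.

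**2. Power inside a subset** (noncentral t, difference 3, SD 3.8):

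| Per arm | Power |
|---|---|
| 5 | 19.7% |
| 8 | 31.3% |
| 12 | 45.6% |
| 13 | 48.9% |

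A median split of 25 per arm leaves 12 to 13 per arm in each half.

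**3. Disagreement between halves when everyone gains 3 days.** The halves contain different people, so their tests are treated as independent.
- Exactly one significant: 0.456 × (1 − 0.489) + 0.489 × (1 − 0.456) = 0.233 + 0.266 = 0.499.
- Both significant: 0.456 × 0.489 = 0.223.

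This depends little on the exact power. With power p in each half, the disagreement rate is 2p(1 − p), which is at least 2 × 0.3 × 0.7 = 0.42 for any p from 30% to 70%. A moderate gain in precision from baseline adjustment would therefore not remove it.

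**4. At least one significant subset when ketamine has no effect.** If k tests were independent, the rate is 1 − 0.95^k. Because the four factors divide the same participants, the rate was also simulated: 50 participants, 4,000 trials per scenario, factors unrelated to each other, and t-tests wherever each arm had at least two people.

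| Subtypes | Botox/CGRP users | Tests (k) | If independent | Simulated |
|---|---|---|---|---|
| 2, equal | 50% | 8 | 33.7% | 26.7% |
| 3 (50/30/20%) | 50% | 9 | 37.0% | 29.3% |
| 5 (50/20/10/10/10%) | 30% | 11 | 43.1% | 32.1% |
| 5, equal | 50% | 11 | 43.1% | 35.3% |

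**5. The same checks for interaction tests.**
- Four tests at 0.05: 1 − 0.95⁴ = 18.5%. Simulated in the same scenarios: 18.3% to 19.8%.
- Power to detect effects that differ by 3 days between two equal halves: SE = 3.8 × √(4/12.5) = 2.15 and 3/2.15 = 1.40. With 46 degrees of freedom this is 27.7%.

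**The case against.** The strongest reply is that this is a condensed article and a statistical analysis plan may exist. Interaction tests, an exploratory label and a multiplicity rule are usually set there, so their absence is not an error. That stands, and the point does not rest on it. It rests on a sentence that commits to comparisons for which the only methods named do not address effect modification.

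A generous reader could take the comparison across subtypes to mean comparing treatment effects across them. That would be the right aim, but no method listed does it; the fix puts that aim into words.

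A reader might also infer that the plan tests ketamine against placebo at 0.05 in each of eleven subgroups (five subtypes plus three two-level factors) and so carries a fixed false-positive rate. The document does not support this. The 0.05 level appears only in Sample size, for headache days and for average intensity. The five subtypes come from the background. Nothing says that frequency and intensity will be split rather than kept continuous. The error rates above are therefore conditional illustrations.

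Nor does the document treat subgroup results as confirmatory. They appear in neither Objectives nor Hypothesis, there is one primary outcome, and mean differences with 95% CIs are promised for continuous outcomes. This limits the harm to interpretation.

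**Conclusion.** The point holds in this limited form: on either main reading of the sentence, the stated analysis does not test whether ketamine's effect varies by Botox/CGRP use, subtype, baseline frequency or baseline intensity.

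The most robust figure is the 50% disagreement between two halves under a uniform 3-day benefit. It needs only a two-way split into equal halves, the protocol's difference and SD, and a 0.05 threshold. The 27-35% chance of a false-positive subset also needs the assumed number of subtypes, median splits and unrelated factors; factors that overlap in what they measure would lower it.

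The primary comparison is untouched. The change is worth making because it is cheap and prevents a misleading statement about who benefits.

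**What to change.** Reword the sentence so that each baseline factor is assessed by a treatment-by-factor interaction, added one factor at a time to the baseline-adjusted ANCOVA of headache days in days 1 to 28, with the factor's main effect in the model. Specifically:

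- Enter baseline frequency and baseline intensity as continuous terms.
- Enter Botox/CGRP use as yes or no.
- Pool sparse subtypes by a rule fixed before unblinding.
- Report each interaction estimate and the subgroup estimates with 95% CIs, without p-values inside subgroups.
- State that all of these analyses are exploratory and cannot support a claim of efficacy in a subgroup.

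**Cost.** One or two sentences and a few model terms; no new data. Both baseline headache days and headache intensity are already covariates in the additional ANCOVA planned for the primary outcome.

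**Limits.** P-values inside subgroups are given up. Four interaction tests still carry about 18-20% familywise error, and power is only about 28% for a 3-day difference in effect between halves. A non-significant interaction will not show that effects are alike, and a significant one may be chance, so the exploratory label is an essential part of the change.

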## Data monitoring

### Formal committee

An independent Data Safety Monitoring Board (DSMB) whose members have experience in clinical trials has been formed. Monitoring and reporting of adverse events will be conducted throughout the whole trial. If there are concerns about the quality of care, and or the safety of any interventions, the committee will have the authority to stop the trial subject to evaluation by the UHN Research Ethics board.

### Interim analysis

There will be no planned interim analysis.

### Safety/harms

Monitoring and reporting of adverse events will be conducted from the time of consent to trial entry until the end of the trial. Adverse events will be documented in the patient file and electronic case report form and reported to the UHN REB.

#### Auditing

Formal audits will be performed at the request of the DSMB or UHN REB. Representatives of the IREB and Health Canada may look at the trial records and at personal health information to verify that the information collected for the trial is correct and to make sure the trial is following proper laws and guidelines.

The sponsor must ensure that investigator(s)/institution(s) will permit trial-related monitoring, audits, Institutional Review Board/Independent Ethics Committee (IEC) review, and regulatory inspection(s), providing direct access to source data/documents.

## Ethics and dissemination

### Research ethics approval

This trial will be conducted in accordance with the ethical principles outlined in the Declaration of Helsinki, the protocol, Good Clinical Practice guidelines, and applicable regulatory requirements. The trial is approved by REB of UHN and Sinai Health System, and Health Canada. Full written informed consent will be obtained from the participants by the research team (Additional file 2: Appendix 2). This trial has been registered on the ClinicalTrials.gov website (NCT05306899), and the results will be reported per SPIRIT guidelines. Before any changes to the trial are implemented, besides those to eliminate an immediate hazard to trial participants, an amendment to the trial will be submitted for review and approval by the IREB. There is no plan for ancillary studies.

### Criteria for subject withdrawal

Subjects have the right to withdraw from the trial at any time, without providing a reason. In the event that a subject decides to prematurely discontinue from the trial, they will be asked if they can still be contacted for further information. This will be documented accordingly. If the subject has already received the trial medication prior to withdrawal, the subject will be requested to be contacted for a safety follow-up visit.

When applicable, subjects should be informed of the circumstances under which their participation may be terminated by the investigator without their consent. The investigator may withdraw the subjects from the trial in the event of intercurrent illness, adverse events, lack of compliance, or at the request of the Institutional Review Board.

### Ancillary and post-trial care

No additional provisions will be made for post-trial care, and routine clinical care will be provided by the participant’s primary physician. If the patient suffers harm as a result of a study intervention, appropriate follow-up care will be provided as indicated.

### Dissemination policy

Trial results will first be disseminated at the local, national, and international conferences and submitted for publication in a peer-reviewed journal. Authorship will be in accordance with the International Committee of Medical Journal Editors guidelines.

## Discussion

Despite recent evolutions in the pharmacological and interventional management of CDH patients, many patients remain refractory to these treatments and/or cannot afford them. Recent evidence shows that infusions of ketamine in high doses and a prolonged duration of treatment could have a positive effect on refractory chronic pain [10], but the quality of evidence for efficacy in CDH is low [17].

This trial aims to investigate the efficacy of high-dose ketamine infusions for chronic daily headaches, by comparing a 6-h high-dose ketamine infusion to placebo. Fifty-six participants will be included and will be divided between the two groups. Participants and assessors will be blinded to the treatment allocation. Data on the frequency and intensity of headaches, mood, activity, sleep, quality of life, and safety of ketamine will be collected from baseline up to 84 days after the intervention.

This trial has several novelties. It is the first trial investigating the impact of a 6-h high-dose intravenous ketamine infusion on the intensity and frequency of CDH in a randomized, double-blinded, placebo-controlled manner. Furthermore, ketamine has been demonstrated to have an effect on sleep and mood and therefore improve the patient’s quality of life [33]. This will be the first trial assessing the impact of ketamine on multiple pain-associated domains by use of validated questionnaires and wearable technology.

Although recent data shows that infusions of ketamine of 1 mg.kg^−1^ .h^−1^ are associated with greater and sustained pain relief as compared to one-off bolus and low-dose infusion regimens, the adverse effects of ketamine are common and could limit dose escalation [8]. Ketamine is associated with adverse psychomimetic, cardiovascular, and gastrointestinal effects resulting from its activity on a variety of substrate receptors including NMDA, acetylcholine, opioid, monoamine, and histamine receptors [8]. The incidence of reported ketamine-induced adverse effects in the recent literature is high, regardless of the type of administration or dose, and has mostly included psychomimetic effects. Most adverse effects were mild and resolved after decreasing the dose or ending the treatment [17].

To limit the incidence of adverse effects in this trial and beyond, these infusions should only be performed by properly trained personnel in a highly monitored environment, which facilitates early detection of issues and prompt treatment. Secondly, all our participants will be treated with benzodiazepines and high-dose anti-emetics to limit the incidence of psychomimetic and gastrointestinal side effects.

This trial will help to identify if ketamine is an effective and safe alternative for headache treatment. The investigators hope the knowledge from this trial will be widely implemented to improve patients’ health and quality of life.

## Trial status

Protocol version and date: version 3.0, August 16, 2022

Date of start of recruitment: August 14, 2022

Estimated end of recruitment: October 1, 2023

Estimated trial completion date: February 1, 2024

## Data Availability

Following the completion of data entry, only the trial investigators and trial coordinators will have access to the final trial dataset.

## Abbreviations

ADR(s): Adverse drug reaction(s)
AE(s): Adverse event(s)
BPI: Brief Pain Inventory
CADDS: Clinician-Administered Dissociative States Scale
CDH: Chronic daily headaches
CGRP: Calcitonin gene-related peptide
CM: Chronic migraine
DHD: Daily headache diary
EQ-5D: EuroQoL – 5 Dimension
EuroQol: Group measurement of health status
GAD-7: Generalized Anxiety Disorder-7 items
HC: Hemicrania continua
HIT-6: Headache Impact Test-6 item
IMP: Investigational medical product
MIDAS: Migraine Disability Assessment
MOH: Medication overuse headaches
MRP: Most responsible physician
NA: Not applicable
NDPH: New daily persistent headache
NMDA: *N*-methyl-d-aspartate
NRS: Numerical Rating Scale
OME: Oral morphine equivalents
PCS: Pain Catastrophizing Scale
PGIC: Patient Global Impression of Change
PHQ-9: Patient Health Questionaire-9
PI: Principal investigator
PSQI: Pittsburgh Sleep Quality Index
SAE: Serious adverse event
TCC: Trigeminocervical complex
TTH: Tension-type headache
TWH: Toronto Western Hospital
UHN: University Health Network
